### Sample size calculation

The sample size was determined based on the priori power analysis through G*Power software version 3.1.9.2. OMERACT-OARSI hip and knee osteoarthritis core outcome set [23] showed that the pain is the most core outcome and the percentage frequency is 94.8% from 1997 to 2017. Furthermore, Guinot et al. [24] reported that the effect size of rTMS for improve pain score in patients with fibromyalgia was 0.24. Therefore, the effect size was set as 0.24 in the present protocol. In the calculations, ANOVA repeated measures between factor was chosen, effect size 0.24, alpha 0.05, power 0.80, number of groups 4, number of measures 6, and the sample size was calculated as 116. Taking into account a conservative anticipation of a 20% drop-out rate, the final sample size will therefore be 37 in each group, with a total of 148 subjects.

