#### Secondary outcomes: Magnetic resonance imaging (MRI)

MRI scan will use a 3.0-T GE scanner (General Electric, Milwaukee, WI, USA) with an eight-channel phased-array head coil at the Medical Imaging Department of Shanghai Seventh People’s Hospital in China. Two independent MRI scans who are radiologists trained in brain MRI measurements and having ten years of work experience will be performed on each participant at baseline and after the 12-week intervention. Before the MRI evaluation, the scanner will require the participant to rest for 10 min and participants will be asked to stay awake with eyes closed during the entire MRI scan.

Resting-state functional MRI images (Rs-fMRI) will be acquired with the following parameters: TR = 2100 ms, TE = 30 ms, flip angle = 90°, voxel size = 3.125 mm × 3.125 mm × 3.6 mm, 42 axial slices, field of view (FOV) = 200 mm × 200 mm, phases = 230. We also collected high-resolution T1-weighted structural images(T1WI), using a 3D-BRAVO sequence with the following parameters: TR = 8.2 ms, TE = 3.2 ms, flip angle = 12°, FOV = 220 mm 20 mm, Matrix = 256,256, slice thickness = 1 mm [48]. The MRI outcomes include the following: grey matter (GM) density, white matter (WM), subcortical nuclei volumes, cortical thickness; functional connectivity (FC).

The DPARSF (http://rfmri.org/DPARSF) will be used to conduct fMRI data preprocessing [49] and the FSL tools (FMRIB Software Library) will be used to process T1WI structure data analysis [50]. The volumes of neocortical GM, total GM, and WM will be obtained by SIENAX (part of FSL 5.0) [51]. The normalized volumes of subcortical nuclei volumes will be estimated from FMRIB’s integrated registration and segmentation tool (part of FSL 5.0, FMRIB Software Library) [52]. The cortical thickness will be obtained using FreeSurfer.

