## Discussion

KOA is classified as a peripheral joint disease, but changes in sensation-movement and pain are mediated by the central nervous system. Rasch et al.[53]proved that the muscle weakness caused by osteoarthritis is related to decreased joint function and increased pain, and that quadriceps training can increase muscle strength and relieve joint pain. Patients with KOA often exhibit strength deficiencies [1] and altered neuromuscular control [54] compared to those without KOA, which may result in suboptimal load dissipation within the knee. Though the motor output and pain changes resulting from KOA have been well-studied, the central contribution to muscle activity is less well known. In this protocol, we design four groups to prove the therapeutic role of high-frequency rTMS combined with quadriceps strength training compared to quadriceps strengthen training alone in KOA patients with 12-week intervention and explore changes of brain volume and function connection before and after treatment.

There are only two studies to prove the treatment effect when combined noninvasive brain stimulation (tDCS) with exercise has been publicized [55, 56]. However, the design of the trial was inadequate, which used inappropriate randomization procedures had a small sample size. And the evaluation is only limited to the change of pain in KOA. Thus, we designed a stricter study to explore the dual clinical effects of reducing pain and muscle strength when the neuromodulation of the M1 with high-frequency rTMS combined with quadriceps strength training in KOA. In addition, to the best of our knowledge, this will be the first single-blind study on rTMS in KOA. Moreover, we will also analyze the correlation measurements between the primary outcomes (VAS, TQPEAK) and secondary outcomes (MEP, FC). Furthermore, the study’s exclusion criteria are relatively strict which will exclude many patients. In this case, it is possible to ensure that our experimental results have a certain degree of accuracy and validity.

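### Grey and white matter volumes are to come from a single-scan tool although the aim is 12-week change; pairing each participant's two scans would give more precise change estimates

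*Protocol article*

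**What the plan says.** The section on MRI outcomes names a tool for each structural measure.

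- Tissue volumes: "The volumes of neocortical GM, total GM, and WM will be obtained by SIENAX (part of FSL 5.0").
- Subcortical nuclei: "The normalized volumes of subcortical nuclei volumes will be estimated from" a registration and segmentation tool in the same FSL package.
- Thickness: "The cortical thickness will be obtained using FreeSurfer".

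The same section says that scans "will be performed on each participant at baseline and after the 12-week intervention". The Discussion gives the purpose of the imaging: to "explore changes of brain volume and function connection before and after treatment".

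MRI is a secondary outcome under Mechanism of action; the primary outcome there is motor cortex excitability. The article states no scan-rescan error and no expected 12-week change for any volume. The sample size is derived from pain.

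**The concern.** The quantity of interest is a within-person difference between two scans, but the tool chosen for grey and white matter returns a volume for one scan at a time. That SIENAX works on a single time point is a property of the named method; the article does not say it. When two separately processed volumes are subtracted, the segmentation and scaling error of each enters the difference. Over 12 weeks the true change in total tissue volume could be small relative to that error.

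At stake is how far the volume results can be interpreted. If error dominates the change score, failing to find a difference between arms says little about whether tissue volume changed. Nothing in the sample size offsets the loss, because no imaging outcome entered it.

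**Working it through.** **1. The plan's own figure, to fix the number of completers.** The Sample size calculation section gives: "ANOVA repeated measures between factor was chosen, effect size 0.24, alpha 0.05, power 0.80, number of groups 4, number of measures 6". The between-factor F test has noncentrality N·f²·m/(1 + (m − 1)ρ) with 3 and N − 4 degrees of freedom. The correlation ρ is not stated; 0.5 is assumed.

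- N = 116: noncentrality = 116 × 0.0576 × 6/3.5 = 11.45; power 0.806.
- N = 112: power 0.790.
- Dropout of 20%: 116/0.8 = 145, rounded up to 4 × 37 = 148.

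The stated 116 and 148 are reproduced. Completers per arm: 116/4 = 29, taken here as participants with two usable scans.

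**2. Effect of separate processing, without outside figures.** Let sT be the SD of true change between participants and e the error SD of one scan. If the two errors are independent:

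SD of change = √(sT² + 2e²)

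Reliability of the change score is sT²/(sT² + 2e²), and the required n is multiplied by 1 + 2(e/sT)².

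| e/sT | reliability | multiplier of n | nominal 80% power becomes |
|---|---|---|---|
| 0.25 | 0.89 | 1.125 | 75% |
| 0.5 | 0.67 | 1.5 | 63% |
| 1 | 0.33 | 3 | 37% |
| 2 | 0.11 | 9 | 15% |

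**3. Illustration in per cent of volume.** All values of e and sT here are assumptions. Detectable difference between two arms (80% power, two-sided 5%, no multiplicity correction) = (1.96 + 0.842) × SD × √(2/29) = 0.736 × SD.

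With sT = 0.3%:

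| e | SD of change | detectable difference | power for a true difference of 0.3% |
|---|---|---|---|
| 0.25% | √(0.09 + 0.125) = 0.464 | 0.34% | 69% |
| 0.5% | √(0.09 + 0.5) = 0.768 | 0.57% | 32% |
| 1.0% | √(0.09 + 2.0) = 1.446 | 1.06% | 12% |

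If paired processing achieves e = 0.25% and single-visit processing 0.5% to 1.0%, the loss is a factor of 0.565/0.341 = 1.7 to 1.064/0.341 = 3.1.

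**4. Sensitivity to the assumptions.**

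- sT = 1%: the SDs are 1.06, 1.22 and 1.73, so the loss is only a factor of 1.15 to 1.6.
- sT = 0: the detectable difference is 0.52% to 1.04% for e = 0.5% to 1.0%, against 0.21% to 0.31% for e = 0.2% to 0.3%. The factor runs from 0.52/0.31 = 1.7 to 1.04/0.21 = 5.0, but the upper end needs no true variation at all and pairs the worst single-visit error with the best paired error.
- Errors at the two visits correlated at r: the added variance is 2e²(1 − r). With r = 0.5, e = 0.5% and sT = 0.3%, the SD falls to √(0.09 + 0.25) = 0.583, the detectable difference to 0.43%, and power for 0.3% rises from 32% to 50%.
- The MRI section's wording about two independent scans is unclear. If it meant duplicate scans at each visit, averaging would halve the error variance and give the same 50%.

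**The case against.** The strongest reply is that the size of the problem cannot be shown from the document. It gives neither a scan-rescan error nor an expected change, and if e is a quarter of sT the reliability is 0.89 and little is lost. Using one scanner and sequence at both visits may also make part of the error repeat and cancel. This stands: the direction of the effect is certain unless the errors cancel completely, but its size is not.

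Three stronger readings are tempting, and the document does not support them.

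- *All brain outcomes are affected.* SIENAX bears only on grey and white matter volumes. Functional connectivity is untouched. For cortical thickness and subcortical volumes the article merely does not say whether the two visits are linked. Nothing in it excludes FreeSurfer's longitudinal stream, and an article may leave such settings to the full protocol.
- *The mechanism claim depends on these volumes.* Motor cortex excitability is the primary mechanism outcome, and the planned correlations use MEP and functional connectivity. The Discussion describes the volume work as exploratory, so a null result there would not settle the mechanism question.
- *The comparison between arms is biased.* With randomised arms and one scanner, the error is expected to be the same in each arm. It costs precision only, and VAS is not involved.

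**Conclusion.** The point holds for neocortical grey matter, total grey matter and white matter volumes. The protocol names a single-scan estimator where the target is change between two scans. This is a stated choice of method, not detail left to a later document. The consequence is lower precision in secondary, exploratory outcomes, and null results that are hard to read.

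Under the assumptions sT = 0.3%, independent errors and 29 completers per arm, the detectable difference is 0.57% to 1.06% rather than 0.34%. A reader might infer a fixed two- to five-fold loss of sensitivity. That is not supported: five-fold needs zero true variation and the most favourable pairing of errors, and the loss shrinks as true variation grows. This is a minor but inexpensive improvement.

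**What to change.** In the MRI section, state that for the 12-week comparison each participant's baseline and week-12 T1 scans are processed as a pair in FreeSurfer's longitudinal stream, and that grey and white matter volumes are taken from it. State that cortical thickness uses the same stream. Keep SIENAX for describing volumes at baseline.

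SIENA, the related FSL tool for two scans, is not a direct substitute. It gives whole-brain percentage change, not separate grey and white matter volumes, and it has no baseline value to adjust for.

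The change needs revised wording and more computing time, but no new scans, visits or software. The drawbacks are that processing must wait until both scans exist, and that a rule has to be stated for participants with only one scan.

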### Safety and adverse events

Every adverse event during the study will be recorded and reported by the safety officer. All potential risks during the study are listed on the participant’s Informed Consent Form. All of them will complete an adverse effects questionnaire for TMS and MRI after intervention.

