### Recruitment, enrollment and randomization procedures

All patients with KOA will be recruited from the orthopedics or joint surgery department of Shanghai Seventh People’s Hospital in China and communities around the hospital. Recruitment methods will include posters, online advertisements, and leaflets. We will communicate with prospective participants about the study details. After the patients voluntarily sign the informed consent, they will be invited to participate in the study. Recruitment will start from 1 October 2023, until when 148 participants are enrolled.

A total of 148 eligible participants will be assigned to four groups at a 1:1:1:1 ratio using stratified randomization with gender, age and KL grade as factors in this research. The stratified randomization will be achieved as follows: Firstly, participants will be invaded into men and women two groups. Secondly, the two groups will be grouped by age (< 50 and ≥ 50). Lastly, the four groups will be grouped by KL grade (II and III), a total of 8 subgroups. In these eight subgroups, the subjects will be randomly regrouped the QT group, HT group, ST + Q group and HT + Q group. Finally, all four groups will be regrouped into four new groups to minimize the bias of the final results. The randomization procedure is performed by an independent research assistant who is not comes into contact with the participant at any point prior to randomization and is not involved in the data collection using Microsoft Excel to generate the random number (https://www.microsoft.com).

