### Allocation concealment and blinding

Allocation concealment will be performed by using sealed, opaque envelopes which will hide a serial number. Additionally, an independent study researcher will open the envelopes in sequence after participants complete all baseline assessments to avoid selective bias. Due to the visibility of the quadriceps strength training intervention, physiotherapists and patients cannot be blind to intervention allocation. Therefore, the blinding will only be applied to the assessors and statisticians who responsible for data collection and final statistical analyses in this study to avoid implementation bias and measurement bias. Importantly, they will not participate in the participant recruitment process.

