### QT Group

In the QT group, the participants will receive 20 min quadriceps strength training intervention by using Biodex Multi-Joint System 3 dynamometer (Biodex Medicalt, Shirley, NY, USA). The 12- week intervention duration period has been chosen based on evidence that at least 12 sessions of supervised exercise are required for exercise to be effective in KOA, with a number of studies demonstrating symptom improvement in KOA after 8–12 weeks of exercise [27]. Thus, 12 weeks should be sufficient to show improvement in this population. We will modify the program according to the user’s manual to reduce the risk to participants and check the device for calibration errors. All participants will be informed how the test will be and its purposes. They will conduct two familiarization sessions before the formal intervention to ensure that they feel comfortable during the exercises and perform the technique correctly. After familiarization sessions, participants will be instructed to sit in an isokinetic dynamometer and the V elcro® fixation straps will be tied around the chest, hip and distal thigh of the training limb to prevent compensatory motion from occurring. The dynamometer axis will be aligned with the canter of the lateral femoral condyle. The lever arm will be adjusted according to the training leg length and the resistance will be applied anterior to the ankle joint. The training knee will be kept at a 90° flexed position and they will be instructed to extend knee at angular velocities of 60°/sec, 90°/sec and 120°/sec with 15 repetitions in 3 sets. Rest periods of 30 s between each test extension and 2 min between each velocity will be given. Training will be performed 5 days per week for 12 weeks. A regular physiotherapist will conduct all isokinetic testing with verbal stimuli. Outcome parameters will be assessed by an independent evaluator, who is experienced in handling isokinetic devices [28]. The peak torque (TQPEAK), TQPEAK adjusted for body weight (TQPEAK/BW) and agonist–antagonist (agon/antag) ratio will be the outcomes.

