### Outcomes

Participants will be assessed by other physiotherapists blinded to the group allocation at different time points based on different assessments shown in Table 1. Additionally, baseline age, gender, symptoms, disease severity, duration, previous treatment and medication will be recorded using a questionnaire (in week 0). The primary end-point is the 12 weeks and all side effects during the study also will be recorded in real time.

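### The one structured adverse-effects questionnaire covers TMS and MRI but not quadriceps training, so solicited harms are not comparable between the two treatments

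*Protocol article*

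**What the plan says.** Two statements in the protocol article promise general capture of harms. Safety and adverse events: "Every adverse event during the study will be recorded and reported by the safety officer". Outcomes: "all side effects during the study also will be recorded in real time". Neither is limited to an arm or a type of treatment.

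One structured instrument is named, also under Safety and adverse events: "All of them will complete an adverse effects questionnaire for TMS and MRI after intervention". No counterpart is named for the quadriceps training.

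On exposure to training, the QT Group section says: "Training will be performed 5 days per week for 12 weeks". The Interventions section sets the same frequency and duration for all four groups, and QT, ST + Q and HT + Q all include the training.

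Allocation concealment and blinding states that "physiotherapists and patients cannot be blind to intervention allocation". Drop-out criteria lists an adverse event caused by treatment as a reason for drop-out, and no section names an occasion for the questionnaire when someone stops early.

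**The concern.** Asking about a harm generally finds more of it than waiting for it to be mentioned. Here the plan asks about one treatment's effects and relies on general recording for the other's. The QT Group section itself speaks of lowering risk to participants when it describes the dynamometer programme, so training harms are not a remote possibility.

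The timing adds to this. If the form is given once at the end of the course, it asks participants to recall up to 60 treatments and a baseline scan 12 weeks back, and it has no stated occasion for someone who left earlier.

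At stake is the harms side of the conclusion. The abstract foresees adding high-frequency rTMS to training for these patients if it proves effective. That advice needs harms of rTMS and of training that were collected in the same way.

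**Working it through.** This is mainly a check of text against text, with a little arithmetic for exposure.

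**1. Arm size.** Sample size calculation gives 116 before drop-out and a 20% allowance. 116 / (1 − 0.20) = 145, and the next multiple of four is 148, or 37 per arm. The plan's figure is reproduced. The point does not depend on it.

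**2. Exposure to training.** 5 days × 12 weeks = 60 planned sessions per participant. Three training arms: 3 × 37 = 111 of 148 participants, and 111 × 60 = 6,660 planned sessions. This is exposure outside the questionnaire's stated scope. It is not a count of missed events.

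**3. Timing of the form.** The Interventions section and the abstract use the word for the 12-week programme, and the MRI section speaks of the 12-week intervention when it places the second scan. Scans take place only at baseline and after the 12 weeks, so one form covering both TMS and MRI fits the end of the course best. Against this, the QT Group and HT Group sections also use the word for a 20-minute treatment. Once at the end is therefore the more natural reading, but not the only one.

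**4. Which comparisons are affected.** Let R be the mean number of true rTMS effects per participant and T the mean number of true training effects. Let a be the share recorded when solicited and b the share recorded by general recording only. Assume that effects add, that a and b are the same in every arm, and that effects of the TMS tests and MRI are common to all arms and cancel. Recorded harms are then:

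- QT: bT
- HT: aR
- HT + Q: aR + bT

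The contrasts are:

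- HT − QT = aR − bT. If b is less than a, this tilts against rTMS for reasons of collection alone.
- (HT + Q) − HT = bT. The harm added by training is understated if b is below a.
- (HT + Q) − QT = aR. The share b cancels, so this contrast is less affected. It would be disturbed if rTMS changed the rate of training harms, or if unblinded reporting made b differ between these arms.
- (HT + Q) − (ST + Q): the same form and the same training on both sides, so b cancels again.

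The level bT is too low in all three training arms whenever b is below 1.

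**5. Size.** The document gives no adverse event rate and no rate of drop-out for adverse events, so R, T, a and b are all unknown. The only related figure is the planned drop-out for all reasons: 0.20 × 37 = 7.4 per arm.

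**The case against.** The case on the other side is substantial.

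- **General capture exists.** The safety section's promise to record every adverse event and the outcomes section's promise of real-time recording cover all arms, including training harms. This stands: the questionnaire is not the only route. But both sentences say that events will be recorded, not that anyone will be asked, so the difference in solicitation remains.
- **The form is for everyone.** No arm is exempt, so the unevenness is by treatment rather than by arm as such. This stands, and it is why HT + Q against QT, the trial's main question, is less affected.
- **Losing those with events.** A reader might infer that participants dropped for an adverse event are missing from the safety data, so that rates are biased downwards. The documents do not support this. An event that triggers drop-out has already been noticed and attributed to treatment, and nothing exempts those participants from the form. What remains is that no occasion is named for giving it to them.
- **A reader might put the undercount at 2 to 9 per arm.** That range is only assumed event rates of 5% and 25% times 37 (1.9 and 9.3). It further assumes that every affected participant is dropped and never completes the form, and it disregards real-time recording. The document supports none of this.
- **Other measures pick up some training harm.** The VAS for movement pain and KOOS pain and symptoms are scheduled at 4, 8 and 12 weeks. This stands in part. The VAS covers only the previous week, and neither asks about injury or falls.
- **An article leaves item content to the full protocol.** True, and the form's items are not shown. The point therefore rests on the scope and timing that the article does state.

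**Conclusion.** The point holds in a limited form and is minor. As written, effects of TMS and MRI are solicited and effects of quadriceps training are not. Training effects rest on general recording, in a trial where patients and therapists know the treatment. Solicited harms are therefore not comparable between the two treatments, chiefly for HT against the training arms, and training harms risk under-ascertainment in all three training arms (111 of 148 participants).

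A reader might go further and conclude that harms will be undercounted unevenly across arms. The document does not support that as a fact: it promises to record all events, it gives the same form to everyone, and it offers no rate from which a size could be worked out. The conclusion assumes that the form's content matches its stated scope and that solicited events are recorded more fully than unsolicited ones. The recall problem, though not the gap in scope, also depends on reading the timing as once after the 12 weeks.

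**What to change.** Amend Safety and adverse events in the protocol as follows:

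- Use one questionnaire in all four arms and add items for the training, for example knee pain flare, swelling, muscle injury and falls.
- Give it at the existing 4-, 8- and 12-week visits, replacing the present ambiguous timing.
- Give it also when a participant stops treatment early, for whatever reason.
- Report harms by arm for everyone who received at least one treatment, showing solicited and otherwise recorded events separately.

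The general recording of all events stays as it is. The cost is a few extra items and a few minutes at visits already planned, with a small protocol amendment. Reported event rates will rise, which should be expected and explained when results are presented.
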